## Abstract

**Objective::**

There is an association between frailty and arterial stiffness. However,
arterial stiffness does not uniformly correlate with the spectrum of frailty
states. Both oxidative stress and inflammaging contribute to vascular
ageing. There are no human studies exploring links between arterial
stiffness, oxidative stress, inflammaging and frailty. Our objective is to
investigate arterial stiffness and inflammaging as predictors of frailty
states.

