**Results (data analysis plan)::**

Descriptive statistics for continuous data using means and standard
deviations for normality distributed variables or medians and inter-quartile
ranges for skewed variables will be used. Participants will be categorised
into CFS 1-3, and CFS 4-6. Categorical data will use frequencies and
comparison between groups. Change in frailty between the groups over 6
months will be compared using paired t-test. Simple linear regression will
be done between frailty measures, arterial stiffness, inflammation and
oxidative stress biomarkers. Significance will be at *P* <
.05.

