### Measurements

At recruitment and at follow up, frailty status of participants would be assessed
using the Rockwood/Clinical Frailty score (CFS) and the electronic Frailty index
(eFI) score. The Rockwood/CFS is a frailty assessment spectrum grouped from 1
(very fit) to 9 (terminally ill). The electronic frailty index (eFI) classifies
frailty into 4 groups spanning from fit (eFI < 0.12) to severely frail (eFI
> 0.36). Participants in this study, would be categorised based on their
scores as no-mild frailty (CFS ⩽ 3, eFI ⩽ 0.24) and moderate frailty (CFS 4-6,
eFI 0.24-0.36). The choice of stratifying the study participants into a spectrum
of frailty states from not-frail to mildly frail and moderately frail is based
on the knowledge that progression towards advanced frailty states can be delayed
and/ or reversed if the right intervention is implemented.^31,33,37^

Arterial stiffness will be measured in 2 ways: using Complior^®38^ and
CAVI^®.39^ Assessment of arterial stiffness will be done at room
temperature with the patient supine and after having rested for 10 minutes.
Patients will be asked to refrain from smoking, eating or drinking caffeinated
drinks for 3 hours before measurements and to avoid consuming alcohol for 10
hours before measurements. Participants will be offered reimbursement for travel
expenses.

(a) The Complior^®^ is a non-invasive device which measures Pulse Wave
Velocity and central pressures. The carotid, femoral and radial pulses are
palpated and marked, and measurements are taken between them. The wave forms are
then measured and recorded on the Complior^®^ programme using small
sensors. We will perform at least 2 measurements, and if similar will use the
mean of these. If these differ by more than 0.5 m/s, a third measurement will be
performed. The PWV value should be the median of these measurements.

(b) Cardio-Ankle Vascular Index (CAVI^®^) is another index which
assesses arterial stiffness, this time it uses measurements in all 4 limbs.
CAVI^®^ then equates the stiffness using the pulse wave between the
heart and the ankles. Complior and CAVI measurements will be done by the same
person to ensure consistency. These 2 measurements will be done only once at
baseline and not at follow up since we do not expect any changes within 6
months.

(c) A blood sample will be obtained by a trained research nurse or doctor. The
participant will be asked to give approximately 20 mls of blood (one and a half

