### Statistical analysis plan

Results will be imported into STATA for data cleaning and statistical analysis.
Since this is a pilot study, analysis will be mainly descriptive. Descriptive
statistics for continuous data will be assessed using means and standard
deviations for normally distributed variables, or medians and interquartile
ranges for skewed continuous variables. Analysis would involve looking at
missing data, drop- out rate which would inform sample size calculation for a
future larger study. Categorical data will be summarised using frequencies and
percentages and comparison between the 2 groups (moderate frailty and no-mild
frailty) done using the chi-squared or Fishers exact test.

Where data are not normally distributed these will be log transformed and
presented as geometric means with their 95% confidence interval. Where data are
not normally distributed even after transformation, these will be presented as
median (IQR) and comparisons between groups done using the Wilcoxon rank-sum
test.

The Primary outcome (change in frailty status) will be compared between the 2
groups using the 2-sample independent t test or a simple linear regression.
Other outcome measures will be analysed in a similar way except if these are
skewed when the Wilcoxon rank-sum test will be used. Similarly, a linear mixed
models approach will be used to study the 2 study time points (baseline and
follow up) in the 2 groups. All tests will be 2 sided and significance will be
set at *P* < .05.

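### The abstract promises predictors of frailty states, but the simple regression it names has no stated outcome time point and no baseline frailty term, so it cannot separate prediction from carried-forward correlation (low severity).

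*Protocol article*

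**What the plan says.** - **Objective (abstract).** The aim is to "investigate arterial stiffness and inflammaging as predictors of frailty" states.
- **Analysis linking markers to frailty (abstract, data analysis plan).** "Simple linear regression will" "be done between frailty measures, arterial stiffness, inflammation and" oxidative stress biomarkers. The sentence does not say whether the frailty measure is the baseline value, the 6-month value or the change, and it names no covariate.
- **Statistical analysis plan section.** "The Primary outcome (change in frailty status) will be compared between the 2" frailty groups by t test or simple regression. "Other outcome measures will be analysed in a similar way except if these are" skewed. A linear mixed "models approach will be used to study the 2 study time points (baseline and" follow-up) in the two groups. No stiffness or biomarker predictor is mentioned in any of these.
- **Timing (Measurements).** For frailty: "At recruitment and at follow up, frailty status of participants would be assessed". For Complior and CAVI: "These 2 measurements will be done only once at" baseline. Item (g) repeats every other baseline measurement at 6 months.
- **Framing in the body.** The Study objective, the Hypotheses with the research question, and the Study Design section speak of an objective measure of frailty and of association, not of prediction.

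**The concern.** A claim that a marker predicts frailty over 6 months is normally read as saying that it tells us something about later frailty beyond what present frailty already tells us. A one-predictor regression cannot show this. Frailty at 6 months is likely to resemble frailty at baseline closely, so any marker that correlates with frailty today will also correlate with frailty at 6 months, even if it says nothing about who gets worse.

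The stated purpose of the pilot is to inform a larger multi-centre study of these links. A carried-forward correlation reported as prediction could give that study a misleading picture of which markers are worth following. The design already collects what is needed to separate the two: stiffness and blood markers at baseline, and frailty at both visits.

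**Working it through.** **The plan's own figure.** There is no power calculation to reproduce. The dropout inflation is correct: 40 / (1 − 0.20) = 50. The check below uses the 40 completers and the stated two-sided 0.05 level.

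**Possible outcomes of the named regression**
1. *Baseline frailty.* Marker and outcome are measured at the same visit. The result is cross-sectional and nothing is predicted.
2. *6-month frailty.* The slope contains the baseline correlation carried forward.
3. *6-month change.* Change in frailty is the declared primary outcome, so this reading is possible. Carry-forward is largely removed, but there is no adjustment for regression to the mean.

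**Model A: the marker adds nothing given observed baseline frailty.** Let r be the correlation of marker and baseline frailty, and s the correlation of baseline and 6-month frailty. Neither is in the protocol; r = 0.3 to 0.5 and s = 0.7 to 0.9 are assumed, with a continuous normal frailty score.
- Correlation of marker with 6-month frailty = r × s. With r = 0.3, s = 0.7: 0.21. With r = 0.5, s = 0.9: 0.45.
- Correlation of marker with change = −r × √((1 − s)/2). With r = 0.5, s = 0.7: −0.5 × √0.15 = −0.19. The sign is negative, so a marker that is higher in frailer people would look protective.
- Rejection rate, Fisher approximation: Φ(atanh(c) × √(n − 3) − 1.96), where c is the size of the correlation. For c = 0.21: 0.213 × 6.083 = 1.297, giving 25%. For c = 0.45: 0.485 × 6.083 = 2.948, giving 84%.

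Simulation (20,000 runs per cell, n = 40) agrees:

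| r | s | 6-month frailty on marker alone | with baseline frailty added | change on marker, unadjusted |
|---|---|---|---|---|
| 0.3 | 0.7 | 26.1% | 4.9% | 11.0% |
| 0.3 | 0.8 | 32.3% | 4.7% | 9.1% |
| 0.3 | 0.9 | 39.5% | 5.0% | 7.1% |
| 0.5 | 0.7 | 60.8% | 4.8% | 22.2% |
| 0.5 | 0.8 | 74.1% | 4.9% | 16.8% |
| 0.5 | 0.9 | 85.2% | 5.1% | 10.6% |

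**Model B: the marker relates to true frailty, each visit's score carries measurement error, and the marker is unrelated to change.** Assumed: correlation with true frailty ρ = 0.3 to 0.5, single-visit reliability R = 0.8 to 0.9, and a small random true change. Simulation (5,000 runs per scenario, n = 40):

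| ρ | marker alone, R = 0.8 | marker alone, R = 0.9 |
|---|---|---|
| 0.3 | 37% | 43% |
| 0.4 | 61% | 67% |
| 0.5 | 82% | 88% |

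With baseline frailty added, the rate is 6% to 16% across scenarios. With change as the outcome it is 4% to 5%.

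A rough check for ρ = 0.5, R = 0.9, ignoring the small true change: ρ√R = 0.474; atanh 0.474 × 6.083 = 3.14; Φ(3.14 − 1.96) = 88%.

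**Together.** Marker alone: about 26% to 88%. Baseline-adjusted: about 5% to 16%. Unadjusted change: about 4% to 22%. Adjustment is the better calibrated under Model A, and change under Model B.

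**The case against.** **The target may be association.** The word predictors in this sense occurs only in the abstract's objective, while the body speaks of association and of an objective measure of frailty. For that aim, a marker's correlation with frailty state is the quantity of interest, and adjusting for baseline frailty would remove much of it. This stands, and it is why rewording the abstract is a full remedy.

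**The high rates are not false positives for association.** A reader might infer that up to 88% of such studies would declare a false association. The documents do not support that. The calculations build in a real correlation between marker and frailty, so such a marker does forecast 6-month frailty state. It only adds nothing to knowing baseline frailty.

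**The regression may use change.** A reader might also infer that the prediction objective fails however the abstract is read. That is too strong. Change in frailty is the primary outcome, and the sentence before the regression concerns change over 6 months. On that reading carry-forward is largely gone; what remains is possible bias from regression to the mean, which is absent under Model B.

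**Details may sit in a fuller plan.** The article does not list the terms of the mixed model, and a covariate list could be held elsewhere. Silence on these is no fault. The point rests on what is stated: an objective of prediction paired with a simple regression.

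**No selection rule is stated.** Nothing says that markers enter the larger study on P < .05, and the analysis is called mainly descriptive. This lowers the severity.

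**Conclusion.** The mismatch is real and of low severity. The abstract states a prediction objective. The analysis it names for linking markers to frailty is a one-predictor regression with no stated outcome time point and no baseline frailty term. The group comparisons and the mixed model, as described, take frailty group as the explanatory variable and do not fill the gap.

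For prediction beyond baseline frailty, the direction of the problem does not depend on the chosen values as long as the marker and 6-month frailty both correlate with baseline frailty. The size does depend on them: the rates rest wholly on the assumed correlations and reliabilities, 40 completers and a continuous frailty score. Which of the adjusted and change-score analyses is the better calibrated depends on an error structure that the protocol gives no means to judge.

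**What to change.** Choose one of two routes before results are seen.

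1. **Keep the prediction objective.** Regress the 6-month value of each frailty measure used on each baseline stiffness index or marker, with the baseline value of the same frailty measure as a covariate. Report the estimate with its 95% confidence interval. Show the regression of 6-month change on the same marker as a sensitivity check, and interpret the two together.
2. **Keep the simple regressions.** Change predictors to correlates of frailty states in the abstract's objective, in line with the Study objective, Hypotheses and Study Design sections, and state which time point of the frailty measure is used.

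The cost is wording and, for the first route, one degree of freedom per model in about 40 completers. No new data are needed, since frailty is already measured at both visits and the markers at baseline.

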**Methods::**

An observational longitudinal cohort study will be used to examine the
association between arterial stiffness, oxidative stress and inflammation in
50 older adults (⩾70 years) with clinical frailty scores (CFS) ⩽6 over 6
months. All study measurements will be taken at baseline. Frailty assessment
will include hand-grip strength, timed-up and go test, mini-mental state
examination, geriatric depression scale and sarcopenia using body
composition measurements with Tanita^®^. Arterial stiffness
measurements will include carotid-femoral pulse wave velocity (cfPWV) and
carotid-radial pulse wave velocity (crPWV) using Complior (Alam Medical,
France). CAVI device will measure Cardio-ankle vascular index and ankle
brachial index (ABI). Oxidative stress blood markers nitrotyrosine (NT) and
8-hydroxy-2’-deoxyguanosin (8-oxo-dG) and inflammation markers
high-sensitive C-reactive protein (hs-CRP) and interlukin-6(IL-6) will be
measured at baseline and 6 month along with lipid profile and glycated
haemoglobin.

**Results (data analysis plan)::**

Descriptive statistics for continuous data using means and standard
deviations for normality distributed variables or medians and inter-quartile
ranges for skewed variables will be used. Participants will be categorised
into CFS 1-3, and CFS 4-6. Categorical data will use frequencies and
comparison between groups. Change in frailty between the groups over 6
months will be compared using paired t-test. Simple linear regression will
be done between frailty measures, arterial stiffness, inflammation and
oxidative stress biomarkers. Significance will be at *P* <
.05.

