tablespoons), plasma samples will then be stored at −80°C until they are tested.
All participants will have samples taken to measure markers of oxidative stress
and inflammation in the clinical research laboratory at the University of
Sussex. Inflammatory markers to be measured would include high sensitivity
C-reactive protein (hs-CRP) and Interlukin-6 (IL-6). Markers for oxidative
stress to be measured would include nitrotyrosine (NT) and
8-hydroxy-2’-deoxyguanosin (8-oxo-dG). Inflammation and oxidation profiles will
be measured by ELISA using commercially available assay kits. Samples would be
handled by the research nurse or doctor for storage before being transported to
the research laboratory at the University of Sussex to be assayed together.

(d) Other biochemistry measurements would be recorded from the hospital computer
system which would include lipid profile, thyroid function and full blood count.
Other routine clinical observations to be checked would be blood pressure, body
mass index (BMI) and random blood sugar (RBS).

(e) At recruitment and follow up, cognition of participants would be assessed
using the Abbreviated Mental Test Score (AMTS) and Montreal Cognitive Assessment
(MoCA). These readings would be taken from the patients’ file. Patients with
scores less than 8 on the AMTS and 23 on MOCA will be excluded from the
study.

(f) Measures of frailty to be assessed will include hand grip strength using the
hand dynamometer, timed up and go test (TUGT) and body impedance with the
Tanita.

(g) Participants will be followed up at 6 months for second measurements to be
taken. Prior to follow up visit, participants would be contacted via telephone
call for booking of appointment. All measurements taken during
baseline/recruitment would be repeated except for the arterial stiffness. Snacks
will be provided for the participants after their participation both at
recruitment and follow up and their transportation bill catered for.

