### Sample size

This is a pilot study with no formal sample size calculation done. We aim to
recruit 40 participants who fit the eligibility criteria, but this number will
be adjusted upwards to 50 participants to account for an expected dropout rate
of 20%. We aim to recruit at least 2 participants per week within 5 months. The
selected sample size is considered reasonable for a pilot/feasibility study by
NIHR.^40,41^ Similarly, this is in line with Browne’s rule of thumb
for pilot study sample size calculations which recommends at least 30 subjects
for pilot studies to estimate differences between 2 groups.^42^ It is
further supported by Julious^43^ who suggests that a
minimum of 12 subjects per treatment arm /group is relevant to reduce
imprecision around the estimates of a standard deviation. The chosen sample size
of 50 is a pragmatic approach considering previous studies which used similar
numbers, where 28 frail older adults were compared with 27 robust non-frail
older adults assessing the differences in oxidative stress markers between both
groups.^23^ Participants would be stratified into 2 groups based on
their frailty status as group 1 having no-mild frailty (ie, having a Rockwood
frailty score ⩽3) and group 2 made up of moderate frailty with a Rockwood
frailty score >3 in line with the study’s inclusion criteria. We would aim to
have an equal number of 25 participants in each group.

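### The association regressions are specified as one-predictor models with no confounder named, so shared dependence on age can appear as a stiffness-frailty or marker-frailty link

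*Protocol article*

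**What the plan says.** The regressions that link frailty measures, stiffness and blood markers appear in one place, the abstract's data analysis plan: "Simple linear regression will be done between frailty measures, arterial stiffness, inflammation and oxidative stress biomarkers". The same paragraph sets the significance level at .05, and the Statistical analysis plan section adds "All tests will be 2 sided and significance will be" set at that level.

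The Statistical analysis plan section describes other analyses. The primary outcome, change in frailty status, is compared between the two frailty "groups using the 2-sample independent t test or a simple linear regression". In addition, "a linear mixed models approach will be used to study the 2 study time points" in the two groups, with no covariates listed. The section also says that, this being a pilot, the analysis is mainly descriptive.

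The following bear on adjustment:

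- Age is an entry criterion (70 and above, no upper limit; Eligibility criteria), so it is known for everyone.
- Measurements, item (d), reads "Other routine clinical observations to be checked would be blood pressure, body" mass index and random blood sugar. Blood pressure is therefore recorded.
- Sex is not mentioned as a recorded variable.
- The groups are defined and balanced on frailty only, 25 and 25 (Sample size).
- Complior and CAVI measurements are taken once, at baseline (Measurements).

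**The concern.** The introduction treats stiffness as the defining sign of vascular ageing, names inflammation and oxidative stress as leading factors behind it, and describes inflammaging as the chronic inflammation of later life. It also links the rise in frailty to population ageing. On that account age is the obvious common cause to consider for the variables in these regressions, but the stated model has no place for it.

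This matters because the stated aims go beyond a raw description. The abstract's objective concerns predictors of frailty states, and the Study aim concerns mediating roles in how frailty arises. A significant unadjusted slope cannot be told apart from the plain fact that older people may be stiffer, more inflamed and frailer.

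The follow-up visit does not solve this. Stiffness has only a baseline value, so the mixed model cannot treat it as a repeated outcome. The research question, whether oxidative stress and inflammation are associated with stiffness, therefore falls back on the abstract's regression.

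**Working it through.** **Inputs from the article.** The aim is to "recruit 40 participants who fit the eligibility criteria", a number that will "be adjusted upwards to 50 participants to account for an expected dropout rate" of 20% (Sample size). Tests are two-sided at 5%.

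**The plan's own figure.** 40 / (1 − 0.20) = 50, which agrees with the stated number. No power, effect size or standard deviation is given, so there is no power to reproduce. The check below uses n = 50 (all recruited) and n = 40 (after the expected dropout).

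**Inputs assumed.** The article gives no correlation of any variable with age. A range of 0.2 to 0.5 is assumed, the same for both variables.

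**Step 1: the correlation produced by age alone.** Let x and y correlate with age a at r_xa and r_ya and have no direct link. Then r_xy = r_xa × r_ya:

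- 0.2 × 0.2 = 0.04
- 0.3 × 0.3 = 0.09
- 0.4 × 0.4 = 0.16
- 0.5 × 0.5 = 0.25

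**Step 2: how often a test of the slope rejects.** The unadjusted test uses t = r√[(n − 2)/(1 − r²)] on n − 2 degrees of freedom. The age-adjusted test uses the partial correlation (r_xy − r_xa r_ya)/√[(1 − r_xa²)(1 − r_ya²)] on n − 3 degrees of freedom. Its true value here is 0, since r_xy = r_xa r_ya. A simulation with 20,000 normal samples per scenario gives these rejection rates:

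| Correlation of each variable with age (assumed) | Implied r | n = 50, unadjusted | n = 50, age-adjusted | n = 40, unadjusted | n = 40, age-adjusted |
|---|---|---|---|---|---|
| 0.2 | 0.04 | 5.8% | 5.0% | 5.9% | 5.0% |
| 0.3 | 0.09 | 9.3% | 5.0% | 8.6% | 5.2% |
| 0.4 | 0.16 | 20.2% | 4.7% | 16.9% | 5.4% |
| 0.5 | 0.25 | 42.0% | 4.8% | 34.9% | 5.2% |

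**Step 3: cross-check by Fisher's z.** For r = 0.25 and n = 50, atanh(0.25) × √(50 − 3) = 0.2554 × 6.856 = 1.751. The rejection probability is P(Z > 1.96 − 1.751) = P(Z > 0.209) = 0.417, against 42.0% simulated. The same method gives 0.095 and 0.198 for r = 0.09 and 0.16 at n = 50, and 0.085, 0.166 and 0.342 for r = 0.09, 0.16 and 0.25 at n = 40.

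**Step 4: cost of adjusting.** The smallest significant |r| is t/√(df + t²), where t is the 97.5% point. As an upper bound, take three covariates:

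- n = 50: df 48 to 45. Unadjusted, 2.0106/√(48 + 2.0106²) = 0.279; adjusted, 2.0141/√(45 + 2.0141²) = 0.288.
- n = 40: df 38 to 35. The threshold moves from 0.312 to 0.325.

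Age alone, or age and sex, costs less than this.

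**The case against.** The strongest reply has four parts.

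- **Pilot status.** The study is a pilot with a mainly descriptive analysis, and its objective and research question ask about markers as a measure of frailty and about association. An unadjusted slope is a legitimate first description for that purpose. This stands as far as it goes: it lowers the severity and is a reason to keep the unadjusted slopes. It does not cover significance tests that serve predictor and mediation aims.
- **Condensed article.** A covariate list is commonly left to a fuller plan. This stands for the mixed model, whose fixed effects are not listed. A reader might infer that no adjusted model of any kind is planned, but the silence there does not show that. It does not rescue the association regressions, for which one-predictor models are stated outright.
- **Size.** Everything rests on assumed correlations. Restricting entry to 70 and above may weaken them, and near 0.2 the inflation is negligible. This stands, and the low end belongs in the range.
- **Choice of covariates.** Blood pressure may be partly a consequence of stiffness, and body composition is itself among the frailty measures, so forcing pressure or BMI into the models could remove part of what is being studied. This stands. Age is the one clear confounder.

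Three other stronger readings are not supported. First, the figures above might be applied to the primary outcome, because simple regression is mentioned there too. That analysis compares change in frailty between two groups, which is a different quantity. Second, one might assume that every useful covariate is already collected, but the text shows age, blood pressure and BMI, not sex. Third, one might say that inflated effect sizes will fix the size of the larger study. The Statistical analysis plan section names only missing data and dropout as inputs to that calculation.

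**Conclusion.** The point holds for the association regressions in the abstract's data analysis plan. They are fixed as one-predictor models tested at P < .05, while the article's own account makes age the obvious confounder. If age is the only link and correlates at 0.2 to 0.5 with each variable, a nominal 5% test rejects in about 6% to 42% of studies at n = 50 and about 6% to 35% at n = 40. The problem is negligible at the low end and serious from about 0.4 upward. Including age restores about 5% throughout.

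The range rests on assumed correlations, on linear relations with normal errors, and on there being no direct link. Adjusting for age would not by itself establish mediation; it removes one rival explanation.

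**What to change.** In the association regressions, replace the one-predictor model with one that pre-specifies age as a covariate, and sex if it is recorded. Report adjusted and unadjusted slopes side by side with 95% confidence intervals, and label the unadjusted slopes as descriptive. Blood pressure may be added in a pre-specified sensitivity model for pulse wave velocity. Do not adjust for BMI. State the same models in the abstract and in the Statistical analysis plan section, which at present does not describe these regressions.

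The change is to analysis wording. Age is already known for every participant, and one or two degrees of freedom are lost. If sex is not recorded, it would be one extra item on the case report form.
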